### Outcome parameters

#### 1. Primary outcome measure

The primary outcome measure will be the level of functioning, as assessed with the SF-20[41-43].

#### 2. Secondary outcome measures

The severity of the symptoms will be measured with the PHQ[35] and the SCL-90[44]. Quality of life will be assessed with the EQ-5D[45,46] and the SF-20, both of which are validated tools for the assessment of general health-related quality of life.

In addition to the evaluation of improvement in general functioning, an attempt will also be made to assess the cost-utility of psychiatric consultation compared to CAU. Therefore, an estimate will be made of the direct medical costs and productivity costs. The necessary data collected by means of the Trimbos/*i*MTA questionnaire for Costs associated with Psychiatric Illness (TiC-P)[47,48].

Additional outcome measures will be the MVI-20, a questionnaire assessing fatigue[49] and the ALCOS-12 that assesses general competence, resilience and initiative in an employee[50].

Process measures will be satisfaction of the employee with the OP (VAS) and compliance with the advice given by the consultant psychiatrist.

Baseline measurements will take place before inclusion (T_0_), and follow up measurements will take place at 3 months with the TiC-P and EQ-5D (T_1_) and at 6 months (T_2_).

### Sample size

In the present study, there will be cluster randomization among the OPs, and Multi Level Analysis (MLA) will be performed with OPs at the first hierarchical level and patients at the second level. The SF-20 will be the primary outcome measure for the power calculation, which will be based on the design effect. This is the factor needed to enlarge the total sample size that would be reached the same standard error that would be reached using randomization between patients and a General Linear Model (GLM) analysis in the sample. The formula is[51]: **Design effect = 1+(n-1)ρ_1_**

n = the mean sample size at the second hierarchical level (patient level in this instance) and ρ_1 _= the intra-class correlation

If a GLM with repeated measures would be used in a study with randomization among patients, with a variance of 1.0, then a sample size of 2 × 10 would be needed for a power of 0.90. A variance of 1.0 as intraclass correlation would be acceptable as a presumption if the contrast between the two groups would be rather high, i.e. if the CAU that was provided was different to the consultation intervention provided in the different practices. We presume that this is the case, because psychiatric consultation in addition to OP care, as in the present study, is a new method for the Netherlands that differs substantially from normal standards of care [20]. Under these assumptions, in a MLA study such as this one, with an SD of 1.0, and a mean number of 3 patients per OP, this would result in a design effect of 3, implying that N should be multiplied by 3, compared to the number needed for a power of 0.90 in patient-randomised GLM analysis. If in such a study a standardized difference of 1.0 was detected, a sample size of 2 × 30 completers would be needed in order to detect a clinically relevant significant improvement of 25%, compared to the spontaneous recovery in the control group on the SF-20. This is the sample size that we aim to achieve in this study[52,53].

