**Methods/design:**

This is a two-armed cluster-randomized clinical trial, with randomization among OPs. Forty OPs in two big companies providing medical care for multiple companies will be randomized to either the intervention group, i.e. psychiatric consultation embedded in a training programme, or the control group, i.e. only training aimed at recognition and providing Care As Usual. 60 patients will be included who have been absent from work for 6–52 weeks and who, after screening and a MINI interview, are diagnosed with depressive disorder, anxiety disorder or somatoform disorder based on DSM-IV criteria. Baseline measurements and follow up measurements (at 3 months and 6 months) will be assessed with questionnaires and an interview. The primary outcome measure is level of general functioning according to the SF-20. Secondary measures are severity of the mental disorder according to the PHQ and the SCL-90, quality of life (EQ-D5), measures of Return To Work and cost-effectiveness of the treatment assessed with the TiC-P. Process measures will be adherence to the treatment plan and assessment of the treatment provided by the Psychiatric Consultant (PC) in both groups.

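### The base of 2 × 10 for 90% power cannot be reproduced from the stated inputs, and the 60 completers required equal the 60 patients to be included

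*Protocol article*

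**What the plan says.** All of the calculation stands in the protocol article under Methods/Design, Sample size. It runs in three steps.

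- **Base.** The starting point is individual randomisation: "If a GLM with repeated measures would be used in a study with randomization among patients", and then "with a variance of 1.0, then a sample size of 2 × 10 would be needed for a power of 0.90".
- **Inflation.** The design effect is 1 + (n − 1)ρ. It is evaluated "with an SD of 1.0, and a mean number of 3 patients per OP", with an intra-class correlation of 1.0, and comes to 3.
- **Target.** "If in such a study a standardized difference of 1.0 was detected, a sample size of 2 × 30 completers would be needed", which the section says is the size the study aims for.

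The section gives no significance level, no sidedness, no correlation between the repeated SF-20 measurements and no dropout rate. The Abstract (Methods/design) says "60 patients will be included who have been absent from work". Recruitment of OPs and consultant psychiatrists says 40 OPs will be recruited.

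**The concern.** The only standardised effect size in the section is 1.0, and the target is exactly three times the base. So 1.0 SD is the only effect to which the base figure can be tied. Ten patients per arm is well below what a two-group comparison needs for 90% power at 1.0 SD. The base is carried straight into the final target, so whatever it lacks is carried along.

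The second part is about units. The target counts patients who complete, and the abstract counts patients who enter. Both are 60. Follow-up lasts 6 months and patients may withdraw at any time, so some loss must be expected.

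At stake is whether a reader can tell from the article what power the trial has for its primary outcome, for which difference, and after how much loss.

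**Working it through.** **Inputs from the Sample size section:** 10 per arm; SD 1.0; standardised difference d = 1.0; power 0.90; ICC 1.0; 3 patients per OP. **From other sections:** 60 patients (Abstract); 40 OPs (Recruitment). **Assumed:** two-sided alpha 0.05; ICC 0.01 to 0.20; 20% dropout.

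**1. The plan's own inflation step.** 1 + (3 − 1) × 1.0 = 3, and 3 × 10 = 30 per arm. This reproduces.

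**2. The base without a repeated-measures gain.** Two-sample t-test, noncentral t, noncentrality d√(n/2) = √5 = 2.24 on 18 degrees of freedom.

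- Power at 10 per arm: 0.562 (one-sided 5%: 0.694).
- Needed for 90%: 2 × (1.960 + 1.282)² = 21.0 by the normal approximation, so 22 per arm. The exact t-test gives 22.02, so 23 (power 0.900 at 22, 0.912 at 23). One-sided 5% still needs 18.
- Difference detectable with 90% power at 10 per arm: 1.534 SD.

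**3. What repeated measures would have to contribute.** The residual SD must shrink to 1/1.534 of its value.

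- Baseline-adjusted: √(1 − r²) = 1/1.534, so r = √(1 − 0.425) = 0.76.
- Change score: √(2(1 − r)) = 1/1.534, so r = 1 − 0.425/2 = 0.79.
- At r = 0.5, power at 10 per arm is 0.69 (baseline-adjusted) or 0.56 (change score). At r = 0.7 it is 0.84 or 0.78.

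**4. Correcting the base alone.** 3 × 22 = 66 and 3 × 23 = 69 per arm, or 132 to 138 in total. This keeps the ICC of 1.0 and 3 patients per OP. But 60 patients over 40 OPs is 1.5 per OP; at 3 per OP, 60 patients occupy only 20 OPs.

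**5. Power of the planned size with no repeated-measures gain.** Effective n per arm = (completers/2) / (1 + (m − 1) × ICC), where m is patients per OP. Each range runs from ICC 0.20 to ICC 0.01.

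| Completers | m | Effective n per arm | Power, d = 1.0 | Power, d = 0.8 | Power, d = 0.5 |
|---|---|---|---|---|---|
| 60 | 1.5 | 27.3 to 29.9 | 0.952 to 0.967 | 0.826 to 0.860 | 0.442 to 0.476 |
| 60 | 3 | 21.4 to 29.4 | 0.892 to 0.965 | 0.725 to 0.854 | 0.359 to 0.470 |
| 48 | 1.2 (48/40) | 23.1 to 24.0 | 0.913 to 0.923 | 0.757 to 0.773 | 0.383 to 0.395 |
| 48 | 3 | 17.1 to 23.5 | 0.810 to 0.919 | 0.623 to 0.766 | 0.295 to 0.389 |

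The difference detectable with 90% power is 0.85 to 0.89 SD in the first row and 0.96 to 0.98 SD in the third.

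**6. Dropout allowance.** Included minus completers required: 60 − 2 × 30 = 0. With 20% loss, 60 × 0.8 = 48 complete. Keeping 60 completers would need 60/0.8 = 75 included.

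**The case against.** The strongest reply is that the base is explicitly attached to a repeated-measures model, so 56% describes an analysis the plan did not name. This stands. A correlation near 0.76 to 0.79 would make 2 × 10 correct, and such a value is not impossible. It would be wrong to infer that the design has 56% power on its own assumptions. What can be said is that the figure depends on a high correlation that the text does not give.

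A second reply is that alpha, sidedness and correlation are details a condensed article may leave to the full protocol. Their absence alone would not be a finding. But the article prints a complete chain from inputs to output, and the printed inputs do not give the printed output.

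Third, the difference of 1.0 is stated beside the 2 × 30 figure, not beside the base. Tying it to the base is an inference, supported by the exact factor of 3 and the lack of any other standardised effect.

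Fourth, one might argue that the Analysis section rules out a baseline gain because it does not list baseline SF-20 among the variables entered. The text does not support that: the confounders there are given as examples, baseline measurement is scheduled, and a repeated-measures model can carry the baseline as an outcome.

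Finally, a reader might conclude from step 4 that 132 to 138 patients are required. That follows only if an ICC of 1.0 and 3 patients per OP are kept. An ICC of 1.0 means that patients of the same OP have identical outcomes, and 3 per OP does not match 60 patients over 40 OPs.

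**Conclusion.** The point holds in two parts.

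- **The base figure is not reproducible from the stated SD and difference.** It gives about 56% power without a repeated-measures gain and 90% only with an unstated correlation of about 0.76 or 0.79. This rests on a two-sided 5% level, which is assumed; a one-sided 5% level does not rescue it (69%).
- **There is no dropout allowance.** This rests on the document alone: 60 completers are required and 60 patients are to be included, so any loss misses the stated size.

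The consequence is a poorly supported justification, not a trial shown to be too small. The low base and the extreme ICC pull in opposite directions. With an ICC of 0.01 to 0.20 (assumed), 60 completers are adequate at 1.0 SD if OPs contribute 1.5 patients each. They are about adequate at 3 each (89 to 96%), falling to 81 to 92% with 48 completers. For an effect of 0.5 SD, power is below one half in every case computed, and the article gives no power for any difference below 1.0 SD. It should be fixed.

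**What to change.** Restate the calculation as a whole, not one step of it.

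- Give alpha and sidedness.
- Either state and support the correlation credited, and analyse SF-20 with the matching baseline-adjusted or repeated-measures model, or use a base of about 2 × 22 to 23.
- In the same step, replace the ICC of 1.0 by a plausible range and the 3 patients per OP by the expected cluster size (60/40 = 1.5). Changing the base alone would give 2 × 66 to 69.
- Use one unit throughout, included or completers. State the expected dropout, and give power and detectable difference for 60 included patients after it, at differences of 1.0, 0.8 and 0.5 SD.

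The cost is one rewritten paragraph and a matching line in the abstract. The restatement asks for no additional patients. The price is that the stated power becomes visibly less favourable for effects below 1.0 SD.

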### Recruitment of OPs and consultant psychiatrists

The study has been designed and will be carried out in co-operation with ArboNed, and Arbounie, two companies providing company medical care. Together they cover almost half of the working population in the Netherlands. Within these two companies, 40 OPs from four offices in two regions will be recruited. Four consultant psychiatrists will also be recruited.

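### The design effect of 3 rests on an intraclass correlation of 1.0 and on 3 patients per OP, which conflicts with 60 patients over 40 OPs; the errors are conservative, but the sample size is not validly derived.

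*Protocol article*

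**What the plan says.** The Sample size section gives the inflation formula "Design effect = 1+(n-1)ρ_1", with n the mean number of patients per OP and ρ the intraclass correlation. The starting point is a patient-randomised trial analysed by a repeated-measures model: "with a variance of 1.0, then a sample size of 2 × 10 would be needed for a power of 0.90". The value for ρ follows: "A variance of 1.0 as intraclass correlation would be acceptable as a presumption if the contrast between the two groups would be rather high". The authors consider that condition met because psychiatric consultation differs greatly from usual care. They then combine "with an SD of 1.0" with "a mean number of 3 patients per OP, this would result in a design effect of 3", and at a standardised difference of 1.0 arrive at 2 × 30 completers.

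The counts are stated elsewhere. In the section on recruitment of OPs and psychiatrists, "40 OPs from four offices in two regions will be recruited". In the abstract, all forty are to be randomised and "60 patients will be included who have been absent from work". The section on treatment in the control group allocates half of the OPs to that arm. No section says that some randomised OPs are expected to contribute no patients.

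**The concern.** Two inputs to the design effect do not describe this trial.

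- **The ICC.** A value of 1.0 means that, within an arm, all patients of one OP have the same SF-20 outcome. A second or third patient of that OP would then add no information, and the patient level of the planned multilevel analysis would have nothing to explain. The reason given for the value concerns how different the two treatments are. That bears on the treatment effect, not on how alike one OP's patients are. The wording itself shows a variance standing in for a correlation.
- **The cluster size.** Forty OPs, 60 patients and a mean of three per OP are not compatible as written.

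The factor of 3 is the whole step from 2 × 10 to 2 × 30. Without it, the 0.90 power has no stated basis. The recruitment target per OP also differs twofold, depending on which count a reader believes.

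**Working it through.** **Inputs.** From the Sample size section: DE = 1 + (n − 1)ρ; ρ = 1.0; n = 3; base of 10 per arm at power 0.90; standardised difference d = 1.0. From the abstract and the recruitment section: 60 patients, 40 OPs. Assumed, because the article gives neither: two-sided alpha 0.05, and an ICC range of 0.01 to 0.20.

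**1. The plan's own figure.** DE = 1 + (3 − 1) × 1.0 = 3, and 10 × 3 = 30 per arm. It reproduces. With n = 3, DE equals 3 only when ρ = 1.0, so there is no doubt which ICC was used.

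**2. The three counts.** 60/40 = 1.5 patients per OP. 40 × 3 = 120 patients. 60/3 = 20 OPs.

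**3. Corrected design effect.** Clusters of exactly 1.5 cannot exist, so sizes must vary. For an unweighted patient mean, n is then replaced by the size-weighted mean Σm²/Σm. If patients fall on OPs at random (Poisson, mean 1.5), this is (1.5 + 1.5²)/1.5 = 2.5, so DE = 1 + 1.5 × ICC.

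| ICC | DE, Poisson clusters, mean 1.5 | DE, exactly 3 per OP |
|---|---|---|
| 0.01 | 1.015 | 1.02 |
| 0.05 | 1.075 | 1.10 |
| 0.10 | 1.15 | 1.20 |
| 0.20 | 1.30 | 1.40 |
| 1.0 | 2.5 | 3 (as stated) |

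More uneven recruitment would raise these values. At an ICC of 0.20, though, DE reaches 3 only if the size-weighted mean is 1 + 2/0.20 = 11.

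**4. The base.** For a simple comparison of two means at d = 1.0, n per arm = 2 × (1.960 + 1.282)² / 1.0² = 21.01, that is 22, not 10. With 10 per arm, power is about 0.61 (0.56 by t-test). A repeated-measures gain could close the gap. In an ANCOVA, 21.01 × (1 − r²) = 10 gives r ≈ 0.72. With change scores, 21.01 × 2(1 − r) = 10 gives r ≈ 0.76. No baseline/follow-up correlation is stated.

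**5. What 30 per arm delivers.** At d = 1.0, in a simple comparison, power is Φ(√(n_eff/2) − 1.960) with n_eff = 30/DE.

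- Poisson clusters, ICC 0.01: n_eff = 30/1.015 = 29.6, power about 0.97.
- Poisson clusters, ICC 0.20: n_eff = 30/1.30 = 23.1, power about 0.92.
- Exactly 3 per OP, ICC 1.0: n_eff = 10, power about 0.61 without any repeated-measures gain.

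**The case against.** The strongest reply is that nothing is miscalculated and that both choices are cautious. An ICC of 1.0 is the upper bound, and three per OP exceeds 1.5. On the plan's own base, correcting either one lowers the required number. That stands, and it fixes the direction of the fault. A reader might infer from an invalid design effect that the trial is too small; the figures do not support that for this fault taken alone.

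A second reply is that three could be the mean per contributing OP, with some of the forty recruiting nobody. Some empty OPs are indeed likely. Under the Poisson assumption P(0) = 0.223, about 9 of 40. But that leaves about 31 contributing OPs and 60/31 ≈ 1.9 patients each. A mean of three requires that half of the OPs contribute nobody, and the article does not say so.

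Two further inferences are tempting and fail.

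- Putting 1.5 straight into the formula gives 1.5 at an ICC of 1.0, or 1.005 to 1.10 at 0.01 to 0.20. That assumes equal clusters and is too low.
- One might prefer 40 OPs with few patients each as the more efficient design. That is a design choice, not a correction. With about 9 empty and 13 single-patient OPs, little information would remain for estimating the variance between OPs.

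**Conclusion.** The point holds as an invalid derivation and an internal contradiction, not as a shortfall in sample size. The stated design effect of 3 needs an ICC of 1.0, for which the article offers only an unrelated reason, and a cluster size that its own totals contradict. Under Poisson clusters with mean 1.5 and an assumed ICC of 0.01 to 0.20, the value is about 1.015 to 1.30.

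A reader might infer that the sample could therefore shrink to about 2 × 11 (10 × 1.05 = 10.5, rounded up). The documents do not support this, because the base of 10 per arm rests on an unstated correlation. Starting instead from 21.01 per arm, a design effect of 1.30 gives 27.3, so 28 per arm, close to the planned 30.

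These figures rest on d = 1.0, which is the plan's own large effect, and on the assumed alpha, ICC range and Poisson spread.

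**What to change.** Rewrite the sample size paragraph as follows.

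- State the number of OPs randomised, the number expected to contribute, the patients per contributing OP and the total, so that they agree. If only about 20 OPs are expected to contribute, say so.
- Replace the ICC of 1.0 by a plausible value with a range, for example 0.01 to 0.20, labelled as an assumption. Delete the argument from contrast between the arms.
- Compute the design effect with an allowance for unequal cluster sizes.
- Re-derive the 2 × 10 base in the same step, giving alpha, the comparison tested and any baseline/follow-up correlation relied on.
- Keep the planned 60 and restate the power across the ICC range. Do not use the smaller design effect to reduce the sample.

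Correcting the design effect costs one rewritten paragraph and needs no additional patients or OPs. Whether 60 remains enough after the base is re-derived depends on the effect size and correlation that the sponsor is prepared to defend.

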### Analysis

Intention-to-treat analysis will be performed by means of MLA, with OPs in the primary hierarchical level. Subsequently, at the secondary hierarchical level, patient characteristics influencing the outcome will be analysed. If differences in outcome are found in MLA, the effect size will be estimated by Chi-square analysis and described in Cohen's d[54]. To control for possible skew ness in the randomized groups, as far as the distribution of confounders is concerned, propensity scores will be calculated[55]. Possible confounders, such as age, gender, history of mental disorder, history of treatment, fatigue, resilience, and satisfaction and compliance of the employee, will be entered as variables in the analysis.

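### The effect size is to be estimated by Chi-square, reported as Cohen's d, and only after a positive multilevel test; this does not fit a continuous SF-20 score and overstates d when it is reported

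*Protocol article*

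**What the plan says.** All places are in the protocol article.

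- **Primary outcome measure:** "The primary outcome measure will be the level of functioning, as assessed with the SF-20". No categories, responder definition or cut-off for the SF-20 are given there or elsewhere.
- **Sample size:** the SF-20 is treated as a continuous score, with a repeated-measures linear model as the reference analysis, an SD of 1.0 and a standardised difference of 1.0: "If in such a study a standardized difference of 1.0 was detected, a sample size of 2 × 30 completers would be needed". The same section has "a mean number of 3 patients per OP, this would result in a design effect of 3", which implies an intraclass correlation (ICC) of 1.0.
- **Analysis, main model:** "Intention-to-treat analysis will be performed by means of MLA, with OPs in the primary hierarchical level". MLA is the multilevel analysis.
- **Analysis, effect size:** "If differences in outcome are found in MLA, the effect size will be estimated by Chi-square analysis", with the result expressed as Cohen's d. The sentence refers to outcome in general and does not name the SF-20, but no other sentence says how an effect size will be obtained.

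**The concern.** Two things are wrong with the effect-size sentence.

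**The method does not match the measure.** Cohen's d is a difference in means divided by an SD. A Chi-square analysis of a table works on categories, so the SF-20 would first have to be cut somewhere, and the cut could be chosen after the data are seen. A table-based d then depends on that cut and on the formula used to convert the table to d. The table also treats patients of the same OP as independent, although the plan uses MLA precisely because they are not. The multilevel model already gives an adjusted mean difference with a standard error, so the Chi-square step replaces a suitable estimate with an unsuitable one.

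**The estimate depends on the test result.** The effect size is calculated only if MLA finds a difference, which in ordinary use means a significant one. Estimates that pass this filter are too large on average, most of all when the true effect is smaller than planned. Readers and later meta-analyses would take up this number.

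**Working it through.** The plan gives no figure for this step, so there is nothing of its own to reproduce beyond the sample size that fixes the setting.

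**Setting.** Design effect = 1 + (n − 1) × ICC = 1 + (3 − 1) × 1.0 = 3. The article's 10 per arm × 3 = 30 per arm, which agrees with its 2 × 30.

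**Assumptions, not in the article:** two-sided alpha of 0.05; normal scores; true d of 0.5 and 0.3 as examples below plan; ICC values other than 1.0; a median split for the Chi-square illustration.

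**1. Selection on significance, independent patients.** With 30 per arm, d is significant only if it exceeds t(0.975; 58 df) × √(2/30) = 2.002 × 0.258 = 0.52. No smaller d would ever be reported. Simulating two-group t tests and averaging d over the significant trials:

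| True d | Share significant | Mean reported d |
|---|---|---|
| 1.0 (planned) | 97% | 1.03 |
| 0.5 | 48% | 0.73 |
| 0.3 | 21% | 0.67 |

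**2. Selection on significance, clustered patients.** Simulation of 10 OPs per arm with 3 patients each, tested on OP means:

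| ICC | True d 1.0 | True d 0.5 | True d 0.3 |
|---|---|---|---|
| 0 | 1.02 | 0.72 | 0.64 |
| 0.1 | 1.05 | 0.76 | 0.69 |
| 0.3 | 1.10 | 0.85 | 0.77 |
| 1.0 (the article's value) | 1.30 | 1.10 | 0.96 |

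Entries are the mean reported difference in SD units. At ICC 1.0 and true d of 1.0, about 56% of trials are significant.

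**3. What a Chi-square table would return as d.** With a median split, the proportions above the cut are Φ(−d/2) and Φ(d/2), and phi is their difference.

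- *d = 1.0:* proportions 0.309 and 0.691, phi = 0.383.
  - Phi conversion: 2 × 0.383 / √(1 − 0.383²) = 0.83.
  - Logit conversion: log odds ratio 2 × ln(0.691/0.309) = 1.61, times √3/π = 0.89.
  - Probit conversion: 2 × Φ⁻¹(0.691) = 1.00.
- *d = 0.5:* proportions 0.401 and 0.599, phi = 0.197. The same three conversions give 0.40, 0.44 and 0.50.

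The same data therefore give a d anywhere from 0.83 to 1.00, depending on a conversion that the article does not name, and that is for one assumed cut.

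**The case against.** The strongest reply is that the trial's inference does not rest on this step. MLA decides whether there is a difference, and the Chi-square comes only afterwards. That is right, and it rules out several stronger readings.

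- **Loss of power.** A reader might infer that dichotomising costs the trial power. It does not, because the Chi-square is not the planned hypothesis test. For the same reason, a false-positive rate worked out for an unclustered Chi-square does not describe this trial.
- **A null result without a confidence interval.** A reader might infer this from the conditional clause. The clause governs only the follow-up effect size. Nothing says that the MLA estimate and its standard error will be withheld after a non-significant test, and an article may leave that reporting to the full plan.
- **A fixed attenuation of d.** The value of 0.83 for a true 1.0 holds only for a median split with the phi conversion. The probit conversion of the same table shows no attenuation.
- **Large selection bias at the planned effect.** At d = 1.0 with independent patients or a small ICC it is only a few percent.

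Two further defences are weaker. First, the sentence does not name the SF-20, and a table could suit a categorical outcome. But as the only effect-size rule it must cover the primary outcome, and Cohen's d points to a continuous one. Second, the authors may have meant a likelihood-ratio or Wald chi-square from the model. The text does not say so, and such a statistic would still be a test result, without direction, units or an interval.

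**Conclusion.** The point stands as a defect in how the effect size is estimated and reported. The multilevel significance test, its power and the sample size are untouched. For the primary outcome, the stated rule cannot be carried out as an ordinary Chi-square without an undefined cut, it ignores clustering by OP, and it makes the effect size conditional on the test result.

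The size of the selection effect depends on the truth. With 2 × 30 independent patients and two-sided 0.05, it is about 3% at the planned d of 1.0, but the reported d is roughly 1.5 times the true value at 0.5 (0.73/0.5) and 2.2 times at 0.3 (0.67/0.3). Under the article's own ICC of 1.0 it is 30% even at the planned effect. The loss from dichotomising cannot be fixed at one figure: for a median split and a true d of 1.0 it runs from none to 17%. Selection pushes d up and dichotomising may pull it down; there is no basis for expecting the two to cancel. These results assume normal scores, and that finding a difference means statistical significance. That the sentence covers the SF-20 is an inference, though a firm one.

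**What to change.** In the Analysis section, delete the Chi-square step for the SF-20 and every other continuous outcome, and remove the condition on the test result. In its place, state that:

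- whatever the p value, the adjusted mean difference between arms from the multilevel model will be reported with its 95% CI;
- Cohen's d, with a CI, will be that difference divided by one SD named in advance, either the pooled baseline SD or the total SD from the model (between-OP plus within-OP variance);
- for any binary outcome, a multilevel logistic model with OP as a level will be used and its estimate reported with a 95% CI.

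The cost is analysis wording only. Sample size, randomisation, data collection and the primary test stay as they are.

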### Recruitment of patients

The aim is to include employees who have been absent from work for a minimum of 6 weeks and a maximum of 52 weeks, do not plan to resume work within the coming 6 weeks, and have been screened on either the Patient Health Questionnaire (PHQ) or the Whitely Index.

All patients who visited an OP within the past 6 months will be selected from the medical files, and will receive a letter describing the purpose of the study, together with an informed consent form for the screening procedure and the baseline questionnaires. Patients visiting an OP during the inclusion period will also be invited to participate in the study. They will also receive the informed consent form, together with the baseline questionnaires.

Patients will be included if they reach a cut off score of >15 on the PHQ9[34] or > 3.5 on the Whitely Index[35] and have given informed consent for participation in the study. The Mini-International Neuropsychiatric Interview (MINI.)[36,37] will be administered for the classification of symptoms according to DSM-IV[38]. In the intervention group, the patients selected in this way will have a consultation with a psychiatrist in addition to the treatment provided by the OP; in the control group the patients receive CAU provided by their OP.

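### The analysis text does not name baseline SF-20, on which the sample-size figure appears to depend, and its adjustment list includes two process measures

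*Protocol article*

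**What the plan says.** - **Outcome.** Under Primary outcome measure: "The primary outcome measure will be the level of functioning, as assessed with the SF-20". The form of the endpoint (6-month value, change, or baseline-adjusted value) is not given.
- **Timing.** Under Secondary outcome measures: "Baseline measurements will take place before inclusion". Follow-up is at 3 and 6 months. Only the TiC-P and EQ-5D are named at 3 months, so SF-20 is read here as measured at T0 and 6 months.
- **Sample size.** The starting point is: "If a GLM with repeated measures would be used in a study with randomization among patients, with a variance of 1.0". From this, "a sample size of 2 × 10 would be needed for a power of 0.90". A design effect of 3 leads to the target: "a sample size of 2 × 30 completers would be needed".
- **Analysis.** An intention-to-treat multilevel analysis is planned. On imbalance between the groups: "as far as the distribution of confounders is concerned, propensity scores will be calculated". The section then gives examples of confounders to be entered: age and gender, prior disorder and prior treatment, fatigue and resilience, and the employee's satisfaction and compliance. That makes eight, and the wording leaves the list open. T0 SF-20 is not among them.
- **Process measures.** The section on secondary outcomes classes satisfaction with the occupational physician (OP) and compliance as process measures. Compliance there means following the consultant psychiatrist's advice.

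**The concern.** Two things in the Analysis section are fixed badly.

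First, the sample size starts from a model that uses repeated SF-20 measurements, but the section that sets out the analysis never says how T0 SF-20 enters. If the multilevel model were run on 6-month scores with only the listed variables, the trial would lack the term on which its stated power depends. A propensity score built from the listed variables does not directly address imbalance in SF-20 itself, because SF-20 is not listed.

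Second, the list mixes characteristics at entry with measures of how care went. Compliance with the psychiatrist's advice can exist only after allocation and is part of how the intervention works. The timing of the satisfaction measure is not stated, but as a process measure it too may respond to the intervention. Conditioning on such variables, directly or through a propensity score, can bias the treatment effect. That is a more serious risk than lost precision.

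**Working it through.** **Inputs from the Sample size section:** 10 per arm under patient randomisation, power 0.90, SD 1.0, standardized difference 1.0, 3 patients per OP, intraclass correlation 1.0, 30 completers per arm.

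**Assumed:** two-sided alpha 0.05 (none is stated); the difference of 1.0 also applies to the 2 × 10 step; correlation r between T0 and 6-month SF-20 from 0.3 to 0.7 (none is stated). Power uses the normal approximation.

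**1. The plan's own figure.** The design effect is 1 + (3 − 1) × 1.0 = 3, and 10 × 3 = 30 per arm. This arithmetic is right.

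**2. Where the 10 comes from.** Without baseline, n per arm = 2(1.960 + 1.282)² × (1.0/1.0)² = 21.01, rounded up to 22. Other error rates do not give 10 either: 18 at one-sided 0.05 or two-sided 0.10, and 14 at one-sided 0.10. Using baseline:

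- Baseline as covariate: 21.01 × (1 − r²) = 10 gives r = √(1 − 10/21.01) = 0.72.
- Change score: 21.01 × 2(1 − r) = 10 gives r = 1 − 10/42.03 = 0.76.

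So the figure is reached only with T0 in the analysis and an unstated correlation of about 0.72 to 0.76. Without T0 the same route gives 22 × 3 = 66 per arm instead of 30.

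**3. Power at 30 per arm under the plan's design effect.** Effective n = 30/3 = 10 per arm. SE = √((2/10)(1 − r²)), and power = Φ(1.0/SE − 1.96). The factor 1 − r² is assumed to apply equally between and within OPs.

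| Use of T0 SF-20 | SE | Power for 1.0 SD |
|---|---|---|
| not used | 0.447 | 0.61 |
| r = 0.3 | 0.427 | 0.65 |
| r = 0.5 | 0.387 | 0.73 |
| r = 0.7 | 0.319 | 0.88 |

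**4. Sensitivity to the intraclass correlation.** A value of 1.0 is extreme. With an assumed 0.05 and 3 per OP, the design effect is 1 + 2 × 0.05 = 1.1. Power for 1.0 SD is then 0.96 even without T0. The gain shows at smaller effects: for 0.5 SD, power is 0.46 without T0, 0.57 at r = 0.5 and 0.73 at r = 0.7.

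**5. Do the listed covariates or the propensity score cost precision?** With N = 60 and k = 8 covariates unrelated to outcome, the variance factor is 1 + 8/(60 − 2 − 8 − 1) = 1 + 8/49 = 1.163. Break-even comes when they jointly explain 1 − 1/1.163 = 14% of outcome variance. A simulation with 30 per arm, no clustering, r = 0.5 and 2,000 runs per setting gave these SEs:

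| Variance explained by the eight | Unadjusted | T0 only | Eight covariates or their score |
|---|---|---|---|
| 0% | 0.258 | 0.227 | 0.281 |
| 10% | 0.258 | 0.225 | 0.259 |
| 20% | 0.259 | 0.226 | 0.249 |

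The listed variables lose precision when weakly prognostic and gain when stronger. In each of these settings T0 alone did better.

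**The case against.** The best reply is that the confounders are only examples, in a condensed article, and that a repeated-measures model treats T0 as an outcome occasion, so it would not appear in a confounder list. That stands to this extent: a reader might infer that the plan leaves baseline SF-20 out of the analysis, and the text does not support that. What it supports is a mismatch. The sample size presumes repeated measures; the Analysis section names only the OP and patient levels, an adjustment method and a list, and does not carry the premise forward.

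Other strong readings also go too far:

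- **Effective sample size.** One might compute 60/(1 − r²) and say that 60 patients become 66, 80 or 118 at r = 0.3, 0.5 or 0.7. This presumes an analysis of raw 6-month scores, which the plan does not state, and ignores clustering. Against a change score the variance ratio is (1 + r)/2, so at r = 0.7 the figure is 60/0.85 = 71.
- **Propensity scores as pure loss.** Step 5 shows that any loss is conditional. Nor need imbalance be only chance: OPs are randomised, and some patients are invited when they visit during the inclusion period. If that follows allocation (the order is not stated), selection could differ by arm, which is a reason for some adjustment.
- **Covariates entering twice.** The last sentence of the Analysis section can also be read as naming the inputs to the propensity score.
- **Duration of absence and office.** Eligibility spans a wide range ("absent from work for a minimum of 6 weeks and a maximum of 52 weeks"), but adjusting for this, or for office, is a preference. Leaving them unnamed is not an error.

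None of this answers the inclusion of satisfaction and compliance, which the article names explicitly.

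**Conclusion.** The point holds as a mismatch between two sections plus a faulty covariate list. The 2 × 10 figure needs T0 SF-20 with a correlation of about 0.72 to 0.76, and the analysis text does not name it. Under the plan's own design effect, power at 30 per arm is about 0.61 if T0 is ignored, against 0.65 to 0.88 if it is used with a correlation of 0.3 to 0.7. These figures rest on an assumed two-sided alpha of 0.05, assumed correlations and the plan's intraclass correlation of 1.0; with a small intraclass correlation the loss matters mainly for effects below 1.0 SD. Loss of precision from the covariates or propensity score is established only if they jointly explain less than about 14% of outcome variance. The bias risk from compliance, and possibly satisfaction, depends on none of these assumptions, though its size cannot be computed from the article. The change should be made before data are analysed.

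**What to change.** In the Analysis section, fix the primary model as a multilevel model of 6-month SF-20 on arm and T0 SF-20, with a random effect for OP and a short, closed list of covariates measured at T0. Fatigue and resilience, if kept, should be T0 values, since their questionnaires also serve as outcomes. Remove satisfaction and compliance from the primary model and from any propensity score. Keep propensity scores, if at all, as a labelled sensitivity analysis. State in the Sample size section the correlation that the 2 × 10 assumes, so that the two sections agree.

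The cost is wording and a few degrees of freedom. T0 measurements are already planned, so no new data are needed.
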